## Abstract

**Background:**

Stress urinary incontinence (SUI) is a subtype of urinary incontinence that occurs more commonly amongst women. The pelvic floor muscle training (PFMT) is considered the gold standard for treating SUI. Another technique called the Knack postulated that pre-contraction of the pelvic floor muscles (PFM) during activities of increasing intra-abdominal pressure prevents urinary loss. Currently, there are no studies supporting the Knack for the treatment of SUI. Thus, the aim of this study is to test the hypothesis that voluntary pre-contraction of PFM can treat SUI. For this purpose, the following parameters will be analysed and compared amongst (1) the Knack, (2) PFMT and (3) the Knack + PFMT groups: urine leakage as assessed by the pad test, urinary symptoms, muscle function, quality of life, subjective cure, adherence to exercises in the outpatient setting and at home and perceived self-efficacy of PFM exercises.

**Methods:**

A single-centre, double-blind (investigator and outcome assessor) randomised controlled trial with a 3-month follow-up of supervised treatment and an additional 3 months of follow-up (unsupervised) for a total of 6 months of follow-up. Two hundred ten women with mild to moderate SUI will be included, aged between 18 and 70 years. To compare the primary and secondary outcome measures within and between the groups studied (before and after intervention), the ANOVA statistical test will be used. Primary and secondary outcome measures will be presented as mean, standard deviation, 95% confidence interval and median and minimum and maximum values.

**Discussion/significance:**

This study closes a gap, as voluntary PFM pre-contraction (the Knack) has not yet been included in the physiotherapeutic treatment of SUI, and if shown successful could be implemented in clinical practice.

**Trial registration:**

ClinicalTrials.gov NCT03722719. Registered on October 29, 2018. Study protocol version 1.

**Was this trial prospectively registered?** Yes

**Funded by**: The present study did not receive funding.

**Anticipated completion date:** The anticipated trial commencement and completion dates are October 2018 and October 2021, respectively.

**Provenance:** Not invited. Peer reviewed.

**Human research ethics approval committee:** Research Ethical Board of the Universidade Federal de São Paulo (UNIFESP), Brazil.

**Human research ethics approval number:** 2.517.312.

**Supplementary Information:**

The online version contains supplementary material available at 10.1186/s13063-021-05440-0.

## Background

Stress urinary incontinence (SUI) is defined as an involuntary loss of urine during effortful manoeuvres, such as coughing or sneezing [1] that occurs more commonly amongst women, with a prevalence of approximately 60% [2]. The severity of SUI increases with ageing; 10% of women aged 25–44 had severe incontinence compared with 15% in the age group 45–59 and 33% in the age group 60+ [1]. Urinary incontinence (UI) is a serious medical condition and a social problem because it causes shame and negative self-perception, hinders participation in social activities and impairs the psychosocial wellbeing of patients [3–5].

Conservative and surgical treatment stand out amongst the therapeutic options for SUI. The interest in a conservative approach has increased because it is less invasive and is associated with a lower risk of adverse complications compared to the high cost and risks of surgery [6–8].

Clinical practice guidelines recommend pelvic floor muscle training (PFMT) as the first-line treatment for female SUI (level A evidence) [8–10]. An alternative technique known as the Knack has also been described, which teaches patients to contract the pelvic floor muscle (PFM) before and during efforts. The Knack is a technique that proposes that the patient perform the contraction associated with her activities of daily and professional life (stress activities that increase intra-abdominal pressure, such as coughing, sneezing, laughing, physical activity) to prevent urine leakage [11]. Other studies—in which the expression “PFM functional training” was used—recommend pre-contraction (the Knack) of the PFM not only during coughing but during any activity of daily living that increases the intra-abdominal pressure [8]. The ideal urethral closure pressure to avoid urine leakage has not yet been established. Amongst continent women, PFM activation seems to be an automatic response that does not require any conscious effort [12, 13]. By learning to perform a fast, strong and timed PFM contraction, incontinent women might actively prevent the urethral descent when the intra-abdominal pressure increases [13].

The literature showed the stabilising effects of the descent of the bladder neck during the activities of increasing intra-abdominal pressure with the Knack technique. Peschers et al. evaluated nulliparous women by perineal ultrasound and electromyography during cough with and without voluntary contraction of the PFM. The descent of the bladder neck was significantly less when women were asked to contract PFM before coughing [4.7 mm (± 2.9)] than when coughing without this contraction [8.1 mm (± 2.9)]. The authors concluded that the Knack technique stabilises the bladder neck during increased abdominal pressure [12]. Miller et al. used perineal ultrasound to check bladder mobility when they coughed with and without the knack technique. The mobility of the bladder neck was significantly reduced from 5.4 to 2.9 mm when the voluntary contraction of the PFM was performed [14]. Another study investigated the immediate effect of timing a PFM contraction with the moment of leakage (the Knack) to preempt cough-related stress incontinence and confirms the effect from the Knack as immediate [15].

Currently, only one study tested the efficacy of the Knack technique for urinary incontinence. Miller et al. reported that the voluntary contraction of PFM before and during coughing reduced the urine leakage after just 1 week of training [16]. Despite being a prospective, randomised, single-blind interventional study, the study has limitations, such as the lack of sample size calculation, the intervention time of only 1 week and the fact that it directed the evaluation only to the cough event. With that, the participants were instructed to perform the pre-contraction only before and during the cough, not including other activities in which the increase in intra-abdominal pressure may occur [16]. So, the essential questions in the assessment of this technique are as follows: Does voluntary PFM pre-contraction (the Knack) prevent urine leakage during the performance of activities that increase intra-abdominal pressure? Can it be used alone for SUI treatment?

The aim of this study is to test the hypothesis that voluntary PFM pre-contraction (alone) can be a treatment for urine leakage during efforts. For this purpose, the following parameters will be analysed and compared amongst (1) the Knack, (2) PFMT and (3) the Knack + PFMT groups: urine leakage as assessed by the pad test, urinary symptoms, muscle function, quality of life, subjective cure, adherence to exercises in the outpatient setting and at home and perceived self-efficacy of PFM exercises.

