### Aim and objectives

The aim of the study is to investigate the effects of voluntary PFM pre-contraction alone during activities involving an increase of the intra-abdominal pressure (the Knack) for the treatment of female SUI.

The objectives are to compare the effectiveness of the Knack alone versus PFMT alone and PFMT + the Knack for the following measures:
Objective cure of urine leakage after intervention, defined as leakage of < 2 g (on the 1-h pad test) immediately after the intervention and 6 months after randomisation (primary outcome measure) [17].Lower urinary tract symptoms and impact of UI on the participants’ quality of life immediately after the intervention and 6 months after randomisation. These secondary outcomes will be assessed by means of the 3-day bladder diary, which considers the number of episodes of urine leakage on efforts [18]; the 1-h pad test, which evaluates the severity of urine leakage [17]; the International Consultation on Incontinence Questionnaire – Short Form (ICIQ-SF), which investigates urinary symptoms [19]; and the Incontinence Quality of Life Questionnaire (I-QoL), which is a measure of quality of life [20].Self-perceived efficacy of exercises immediately after intervention and 6 months after randomisation. This parameter will be assessed by means of the Self-Efficacy Scale for Practising Pelvic Floor Exercises [21]; satisfaction and desire to perform some other treatment immediately after the intervention and 6 months after randomisation (participants will be rated “satisfied” when they do not manifest a wish to perform some other treatment and as “dissatisfied” when they do wish to perform some other treatment) [18].PFM strength function as measured by digital palpation (PERFECT scheme) [22, 23], Peritron manometer [24] and pelvic floor dynamometry immediately after the intervention and 6 months after randomisation.

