### Participants

The study population will comprise women with mild to moderate SUI or mixed urinary (MUI). The diagnosis of SUI will be based on the patient’s report of leakage during physical stress and report of the condition that bothered them the most in case of mixed urinary incontinence (stress urinary or urgency incontinence) and confirmed by means of the 1-h pad test (leakage ≥ 2 g) [17]. Leakage up to 10 g will be rated as mild SUI and 11 to 50 g leakage as moderate SUI [17]. The sample will also include women with grade 2 muscle strength (normal contraction with an elevation of the anterior vaginal wall) on the two-finger assessment rated according to the Oxford scale [22, 23].

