### Randomisation/blinding

#### Sequence generation and allocation concealment

Patients who agree to participate by signing an informed consent form will be stratified (to ensure sample homogeneity) into two groups based on the 1-h pad test results. The stratification will be performed according to the severity of SUI (mild leakage ≥ 2 to 10 g; moderate leakage 11 to 50 g) [17]. Next, the patients will be randomly allocated to one of three treatment groups (the Knack, PFMT and the Knack + PFMT). The allocation sequence will be generated by a research assistant ([name]) using a computer-generated random number table (http://randomization.com) [29] with a group ratio of 1:1:1 and will be concealed in sequentially numbered, sealed and opaque envelopes. The envelopes will be kept in a closed locker at the centre to which only the research assistant will have access. The envelopes will be given to the physical therapist ([name]) immediately prior to the first outpatient session.

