#### Primary outcome measure

The primary outcome measure will be the objective cure of UI as assessed by means of the 1-h pad test 6 months after randomisation. For the 1-h pad test, the women will be asked to wear pre-weighed pads and drink 500 ml of sodium-free liquid in < 15 min. After rest, they will be instructed to exercise for 30 min, including walking, climbing up and down five flights of stairs (10×), jumping (10×), coughing vigorously (10×), bending to pick up an object from the floor (10×) and washing hands for 1 min in running water. Before and after the test, the weight of the pad will be measured with a high-precision balance to determine the amount of leakage. For the 1-h pad test, an increase of 1 to 10 g represents mild incontinence and 11 to 50 g represents moderate incontinence. Women with urine leakage ≥ 2 g will be included because the study will be conducted in a tropical country [17]. The objective cure of urine loss after the intervention will be defined as leakage < 2 g. The pad test is considered a relevant tool for the assessment of UI treatment success and has been widely used in this type of study [30–32].

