**Fig. 1 Fig1:**
[figure not shown]
CONSORT flowchart

Descriptive statistics will be performed for sample characterisation. Categorical variables will be expressed as the distribution of frequencies, and numerical variables by means of measures of central tendency and variability. The mean, standard deviation, 95% confidence interval, median and maximum and minimum values will be calculated for the analysis of the primary outcome measure (pad test). The primary outcome measure (pad test) will be compared within and amongst groups (the Knack, PFMT and the Knack + PFMT) (before and after intervention) using an ANOVA. All statistical analyses will be performed using the current version of SPSS software after the last patient undergoes the final assessment after intervention. The same approaches and statistical procedures used for the primary outcome measures will be employed for the analysis of the secondary outcome measures.

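### Before-after tests within each arm are planned on the same footing as the randomised comparison, although they cannot show that the Knack alone treats stress incontinence

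*Protocol article*

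**What the plan says.** **Hypothesis.** The Background (last paragraph) sets out to "test the hypothesis that voluntary PFM pre-contraction (alone) can be a treatment for urine leakage during efforts". The Abstract words the hypothesis in similar absolute terms, and the Background also asks whether the technique can be used on its own as treatment.

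**Objectives.** The Aim and objectives section is comparative: "The objectives are to compare the effectiveness of the Knack alone versus PFMT alone and PFMT + the Knack for the following measures". The Sample size calculation likewise names the comparison of the Knack with PFMT as primary and frames it as non-inferiority.

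**Arms.** Under Sequence generation and allocation concealment, women are "randomly allocated to one of three treatment groups (the Knack, PFMT and the Knack + PFMT"), "with a group ratio of 1:1:1". All three groups receive an active exercise programme.

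**Analysis.** The Statistical analysis section says that the pad test "will be compared within and amongst groups (the Knack, PFMT and the Knack + PFMT) (before and after intervention) using an ANOVA". The Abstract repeats the within-and-between wording, and the same procedures are extended to the secondary outcomes.

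**Entry and cure.** Under Participants, the diagnosis is "confirmed by means of the 1-h pad test (leakage ≥ 2 g"), with 50 g as the upper limit of moderate leakage. Under Primary outcome measure: "The objective cure of urine loss after the intervention will be defined as leakage < 2 g".

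**The concern.** The absolute hypothesis and the within-arm tests invite each other. A significant fall in leakage, or a significant rise in cure, inside the Knack arm reads like an answer to whether the Knack can treat stress incontinence. Such a change has no concurrent control. It mixes any effect of the Knack with natural course, therapist contact and ordinary variation between two pad tests.

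For cure status there is a further problem. Selection at 2 g or more and cure at less than 2 g are complementary, so nobody starts cured and every crossing counts as benefit.

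At stake is the conclusion that could be drawn if the Knack does not hold up against PFMT. The plan would still supply a within-arm p-value, and nothing in the text says that it carries less weight than the randomised comparison.

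**Working it through.** **1. Inputs from the article.** Entry at 2 g or more and up to 50 g (Participants; Table 2). Cure at less than 2 g (Primary outcome measure). 61 women per arm before the allowance for losses, 70 after it: 210 / 3 (Sample size calculation). The article gives neither the retest reliability of the pad test nor the distribution of leakage at entry, so every crossing rate below is an assumption.

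**2. The plan's own figure.** With θ1 = 0.429, θ2 = 0.714, δ = −0.0714, one-sided 5% and 80% power:

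n = (1.645 + 0.842)² × [0.429 × 0.571 + 0.714 × 0.286] / (0.429 − 0.714 + 0.0714)² = 6.183 × 0.4492 / 0.04562 = 60.9, hence 61.

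The figure reproduces with the usual variance term θ2(1 − θ2). It is a between-arm calculation and is used here only for the arm size.

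**3. Before-after test of cure within one arm.** With nobody cured at entry, all discordant pairs lie on one side. For k crossings the exact two-sided McNemar p-value is 2 × 0.5^k.

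- k = 5: p = 0.0625
- k = 6: p = 0.031

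Six of 61 women (9.8%) are therefore enough.

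**4. How often this happens with no treatment effect.** If each woman has chance q of reading below 2 g at follow-up, P(significant) = P(X ≥ 6), where X is binomial (n, q).

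| Assumed q | n = 61 | n = 70 |
|---|---|---|
| 5% | 8% | 14% |
| 10% | 58% | 71% |
| 15% | 91% | 96% |
| 20% | 99% | 99.7% |

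**5. Is that range of q plausible?** This was simulated with log-normal pad weights, no change in true leakage, entry limited to 2–50 g, log-SD 0.9 or 1.2 and retest correlation 0.5, 0.7 or 0.9. The share reading below 2 g at retest was:

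- 7–20% at median 4 g
- 2–10% at median 8 g
- 1–6% at median 12 g

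The size thus depends strongly on how mild the sample is.

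**6. The same question on mean grams, the scale that the planned ANOVA suggests.** In those 18 settings mean leakage rose in 15, and a significant decrease appeared in about 0–7% of arms, against a nominal 2.5% in that direction. A second grid had 24 settings (median 3–20 g, log-SD 1.0 or 1.4, reliability 0.5–0.9). It gave a significant decrease in 0–12% of arms and a significant increase in 0–80%. The 50 g entry ceiling also selects low readings, and this pulls the follow-up mean upwards. These runs contain retest variation only, not natural recovery or attention.

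**The case against.** The strongest reply is that the trial does rest on a randomised comparison. The sentence after the hypothesis says that the parameters will be compared among the three groups, the objectives are comparative, and the sample size is a non-inferiority calculation against a treatment that the article calls first-line. Non-inferiority to an accepted treatment is a legitimate indirect route to the claim. This stands. A reader might infer that the within-arm test is the only comparison bearing on the Knack, or that the lack of an untreated arm is an error. The article supports neither.

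A reader might also infer that a before-after test would look positive whatever happened. Step 6 shows that this fails for mean grams. It can hold for cure status if enough women cross by chance. Nor should the spurious cure rate be set against the 7.14-point margin. The margin is a difference between arms, and retest noise is expected equally in all randomised arms.

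Three further replies have some force.

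- The within-and-between wording may describe a repeated-measures ANOVA with time within and group between, with details left to an analysis plan that is not shown. Even so, the time effect inside an arm has no control, and the text does not rank it below the group comparison.
- Recruitment describes an eligibility pad test before the contraction teaching, and Table 1 lists one at 0 months. If the latter is a fresh reading used as the before value, some selection and teaching effects are already in the baseline, and cure change need not be strictly one-way. The article does not settle this.
- No sentence says that a within-arm gain will be used to claim efficacy. That is true. The point concerns a conclusion left open, not one announced.

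**Conclusion.** The point holds in a limited form. The hypothesis is worded as an absolute effect, the randomised evidence is relative, and within-arm tests are planned with equal standing. A significant within-Knack change could not be attributed to the Knack.

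For cure status the exposure may be large: a chance of false significance of about 8% to 99% for assumed crossing rates of 5% to 20%. This rests on three assumptions: 61 women, the entry reading serving as the before value, and a paired test of cure, which the article does not name explicitly. For mean grams, retest variation alone does not reliably produce a false decrease.

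The active-control design itself is not at fault. The matter is one of wording and of the status given to the within-arm tests, and it should be put right before analysis.

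**What to change.** 1. **Background (last paragraph), Aim and objectives, and the matching Abstract sentence.** State the hypothesis as the effect of the Knack relative to PFMT on objective cure at 6 months, in the non-inferiority form that the sample size section already uses. Keep the comparison with the combination as a further randomised contrast.
2. **Abstract (Methods) and Statistical analysis.** Make the between-arm comparison the only inferential basis for efficacy. Report within-arm changes descriptively, as estimates with confidence intervals and without significance tests. Apply the same rule to the secondary outcomes.
3. **Statistical analysis.** Add one sentence saying that improvement within an arm will not be used to claim that the Knack treats stress urinary incontinence.

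No extra women, visits or arms are needed, so the change is still possible with 185 of 210 recruited. It can be recorded in the registry, as the Trial status section provides for amendments. The cost is fewer tests and a narrower conclusion. The change does not repair the sizing of the randomised comparison. That sizing assumes a difference of 42.9 − 71.4 = −28.5 points, beyond the −7.14-point margin, and is a separate matter.

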### Aim and objectives

The aim of the study is to investigate the effects of voluntary PFM pre-contraction alone during activities involving an increase of the intra-abdominal pressure (the Knack) for the treatment of female SUI.

The objectives are to compare the effectiveness of the Knack alone versus PFMT alone and PFMT + the Knack for the following measures:
Objective cure of urine leakage after intervention, defined as leakage of < 2 g (on the 1-h pad test) immediately after the intervention and 6 months after randomisation (primary outcome measure) [17].Lower urinary tract symptoms and impact of UI on the participants’ quality of life immediately after the intervention and 6 months after randomisation. These secondary outcomes will be assessed by means of the 3-day bladder diary, which considers the number of episodes of urine leakage on efforts [18]; the 1-h pad test, which evaluates the severity of urine leakage [17]; the International Consultation on Incontinence Questionnaire – Short Form (ICIQ-SF), which investigates urinary symptoms [19]; and the Incontinence Quality of Life Questionnaire (I-QoL), which is a measure of quality of life [20].Self-perceived efficacy of exercises immediately after intervention and 6 months after randomisation. This parameter will be assessed by means of the Self-Efficacy Scale for Practising Pelvic Floor Exercises [21]; satisfaction and desire to perform some other treatment immediately after the intervention and 6 months after randomisation (participants will be rated “satisfied” when they do not manifest a wish to perform some other treatment and as “dissatisfied” when they do wish to perform some other treatment) [18].PFM strength function as measured by digital palpation (PERFECT scheme) [22, 23], Peritron manometer [24] and pelvic floor dynamometry immediately after the intervention and 6 months after randomisation.

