Thus, according to the result of the pilot sample, at the 5% significance level, there is no significant difference between the groups in relation to the objective cure rate in the treatment of mild and moderate SUI, assessed by the 1-h pad test. Considering the premises: θ_1_= 42.9% and θ_2_= 71,4% (obtained through the analysis of the pilot sample), *δ* = − 7,14% (10% variation in relation to the response rate of the PFMT group, obtained through literature data [38], *r* = 1 (groups of equal sample sizes), *α* = 5% and *β* = 20% ⇒ power (1 – *β*) = 80%, we obtained a total of 122 patients (61 patients per group). Thus, considering a significance level of 5%, a sample of 122 patients (61 patients per group) has 80% power to show the non-inferiority of the knack technique compared to PFMT in the treatment of mild and moderate SUI, with a non-inferiority margin of − 7.14%, which corresponds to a variation of 10% in relation to the response rate of the PFMT group (gold standard), supposedly equal to 71.4% and assuming that the rate of response of the test group is 42.9%. The sample size calculation was based on the primary objective of comparing the Knack technique (experimental group) with PFMT (control group). However, we have a third group that associates the techniques PFMT + the knack, so, 183 participants will be recruited. It is also necessary to consider possible losses in the sample during the 6-month follow-up period, thus, we assume losses of 0 to 15% based on previously published studies [39, 40]. Thus, we will recruit nine more participants per group, increasing the total number of participants to 210.

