## Discussion

As effort activities typically provoke SUI within milliseconds [42], the focus of physiotherapy PFM training protocols on pre-contraction (the Knack) seems crucial for SUI patients. However, the gold standard SUI physiotherapy concentrates on PFMT. This study aims to distinguish each component of the pelvic floor training and to document its contribution separately; to validate Knack’s manoeuver, that is, investigating voluntary PFM pre-contractions, as a specific component of pelvic muscle training; and to determine its unique effect as a minimalist intervention.

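### The trial was sized for non-inferiority of the Knack to PFMT, but the only stated primary analysis is a three-arm ANOVA that does not test that comparison

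*Protocol article*

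**What the plan says.** Five places in the protocol article bear on which comparison decides the trial.

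- **Background (closing paragraph):** outcomes are to be "compared amongst (1) the Knack, (2) PFMT and (3) the Knack + PFMT groups".
- **Aim and objectives:** the trial will "compare the effectiveness of the Knack alone versus PFMT alone and PFMT + the Knack for the following measures". Objective cure, the primary outcome, heads the list. Both Knack contrasts apply to it and neither is ranked.
- **Sample size calculation:** "The sample size calculation was based on the primary objective of comparing the Knack technique (experimental group) with PFMT (control group"). The hypotheses are for non-inferiority, with a margin of −7.14 percentage points, α = 5% and 80% power. The combination arm then enters only as a third arm of equal size: "we have a third group that associates the techniques PFMT + the knack, so, 183 participants will be recruited". No hypothesis or power is attached to it.
- **Statistical analysis:** the pad-test outcome "will be compared within and amongst groups (the Knack, PFMT and the Knack + PFMT) (before and after intervention) using an ANOVA". Neither Knack versus PFMT as a contrast, nor non-inferiority, nor the margin appears there.
- **Discussion:** "This study aims to distinguish each component of the pelvic floor training and to document its contribution separately".

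The primary outcome section fixes endpoint and time: "The primary outcome measure will be the objective cure of UI as assessed by means of the 1-h pad test 6 months after randomisation", with cure defined as leakage below 2 g.

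**The concern.** The confirmatory question is whether the Knack alone is not unacceptably worse than PFMT. The stated test asks whether any of three arms differs from the others. The two can give different answers in both directions. The ANOVA can be significant because the combination is better while the Knack and PFMT are identical. It can also be non-significant while the data are too imprecise to exclude a loss larger than the margin.

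An analysis plan written from the statistical analysis section would therefore differ from one written from the sample size section. With two unranked Knack contrasts in the objectives as well, the report could rest its conclusion about the Knack alone on a result that does not bear on the comparison the trial was sized for.

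**Working it through.** **1. The sized comparison.** Inputs from the sample size section: θ₁ = 0.429 (Knack), θ₂ = 0.714 (PFMT), δ = −0.0714, α = 5%, power 80%, equal arms. With one-sided z values and the usual variance term:

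n = (1.645 + 0.842)² × [0.429 × 0.571 + 0.714 × 0.286] / (0.429 − 0.714 + 0.0714)² = 6.183 × 0.4492 / 0.04563 = 60.9, i.e. 61 per arm.

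This matches the stated 61. The calculation uses two arms and a margin. The planned analysis uses three arms and no margin.

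**2. What the three-arm test does when Knack = PFMT.** Binary cure was simulated with 61 per arm (400,000 runs per scenario). The global test was the 2-df chi-square, Σ n(pᵢ − p̄)² / [p̄(1 − p̄)], rejecting above 5.99. A one-way ANOVA F test on the 0/1 cure variable gave the same rejection rates. The combination rates, and the equality of the two single arms, are assumptions.

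| Knack = PFMT | Combination | Global test rejects | Knack vs PFMT rejects (two-sided 5%) |
|---|---|---|---|
| 50% | 60% | about 19% | about 6% |
| 50% | 65% | about 38% | about 6% |
| 50% | 75% | about 85% | about 6% |
| 71.4% | 80% | about 18% | about 5% |
| 71.4% | 90% | about 77% | about 5% |

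The last column stays near 5%, as it should when those two arms are equal. The third column is driven by the combination arm.

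**3. What a non-significant global test leaves open.** Suppose the Knack and PFMT are observed exactly equal with 61 per arm. The one-sided 95% lower limit for the difference is −1.645 × √[2p(1 − p)/61].

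- At p = 0.5: −1.645 × √(0.5/61) = −0.149, or −14.9 points.
- At p = 0.714: −1.645 × √(0.4084/61) = −0.135, or −13.5 points.

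Both lie below −7.14 points. If the combination is also similar, the ANOVA is non-significant and non-inferiority is still not shown.

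**4. Family-wise error, only if pairwise tests were used.** Under equality of all arms, two contrasts sharing the Knack arm (correlation 0.5), each tested at an unadjusted two-sided 5%, give 9.1%. All three pairs give 12.2% (studentized range). If pairwise tests follow only a significant three-arm test, the simulated rate under the same null is 4.8% to 5.0%, the same as the global test alone.

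**The case against.** **The plan does name its primary comparison.** The sample size section ranks Knack versus PFMT first, and the objectives merely list both Knack contrasts, so those two can be read together. This stands: the plan is not silent. The fault is that the analysis section does not follow the ranking and the objectives do not repeat it.

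**Hierarchy and multiplicity rules may sit in an analysis plan that is not shown.** This also stands, and their absence is not the point. A stated primary analysis that does not address the stated primary objective is a conflict within the document, and a later plan would have to overrule one section or the other.

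**Rejecting the global null when the combination really differs is a correct rejection.** True. It misleads only if it is read as a result about the Knack, and no section proposes that reading. But no section gives any other test from which to draw the conclusion about the Knack.

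**The rejection rates rest on assumed combination rates.** They do, and the spread from about 18% to 85% is the honest summary. They also treat the outcome as cure or no cure. If the ANOVA is meant for pad weight in grams, they do not transfer, but the mismatch remains.

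**Stronger readings that the documents do not support.** A reader might infer that the plan carries a 9% to 12% false-positive rate. It does not: no pairwise tests are specified, and those figures need two or three ungated, unadjusted tests, each counted as a route to success. They also describe difference tests. For non-inferiority, a positive finding when the two arms are equal is correct. Nor would pairwise tests after a significant global test leave the error rate uncontrolled. With three arms, once one arm differs from two equal ones, only one true null remains. Finally, the combination arm was not an afterthought: the pilot already randomised to all three groups, and only the arm size was copied from the two-arm calculation.

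**Conclusion.** The point holds as a conflict between sections. Non-inferiority of the Knack to PFMT sized the trial, yet the objectives leave that contrast unranked and the only stated analysis of the primary outcome does not test it. Followed as written, the analysis would not answer the primary question. Depending on the assumed benefit of the combination, the global test would be significant in roughly 18% to 85% of trials with the Knack and PFMT identical (61 per arm, binary cure, assumed rates). A non-significant result would not establish non-inferiority.

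The change should be made before analysis. There was still time when the article was written: it reports 185 of 210 recruited and places the analysis after the last patient's final assessment.

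**What to change.** In the objectives and the statistical analysis section, state one confirmatory comparison: the Knack versus PFMT on objective cure (pad test below 2 g) at 6 months. Estimate it from those two arms as a difference in proportions, with a confidence interval judged against the stated non-inferiority margin. Say that it is neither gated on nor replaced by the three-arm ANOVA.

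Label Knack versus combination and PFMT versus combination as secondary, tested in a fixed order after the primary, or as exploratory. Limit the Discussion's claims about separate components to match.

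This costs a few sentences. The downside is that combination-arm results become secondary or exploratory, which fits an arm with no stated hypothesis or power. The change does not settle whether 61 per arm is enough for the non-inferiority test. The assumed difference of 42.9 − 71.4 = −28.5 points lies outside the −7.14 margin, and that needs separate attention.
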